### Intervention

A total of ten sessions lasting 20 min each will be administered to participants over Monday/Wednesday/Friday or Tuesday/Thursday/Saturday (three sessions per week) by a trained physician at the Instituto do Rim (Fig. 1). The tDCS method will use a monophasic continuous current with an intensity of 2 mA for 20 min (Fig. 2). Each patient will be awake and sit in a comfortable chair with back and arm support during the tDCS intervention. tDCS will be performed before the usual session of dialysis.

**Fig. 1 Fig1:**
[figure not shown]
Flowchart summarizing the trial. *According to clinical routine, interventions could be performed on Tuesday/Thursday/Saturday. *VAS* Visual Analogue Scale, *M1* motor cortex, *DLPFC* dorsolateral prefrontal cortex

**Fig. 2 Fig2:**
[figure not shown]
Illustration of electrode replacement. **a** M1 group. The anodal electrode will be placed over the motor cortex and the cathode over the supra-orbital contralateral area (C3/Fp2 montage). **b** DLPFC group. The anodal electrode will be placed over the DLPFC and the cathode over the supra-orbital contralateral area (F3/Fp2 montage). Electrodes will the placed according to 10/20 EEG international system. Electrode size 35 cm^2^ with a current density of 0.057 mA/cm^2^

During the baseline period, patients will be randomized at a ratio of 1:1:1 to receive sham tDCS (sham group), active tDCS of the primary motor cortex (M1 group), or active tDCS of the left DLPFC (DLPFC group). The M1 was chosen because studies show that stimulation of this area is associated with pain improvement [9, 11, 15, 16]. The left DLPFC was chosen because several studies with neuromodulation have shown that stimulating this area is associated with improvement of depression and also induces an analgesic effect in fibromyalgia [9, 15]. The electrodes will be placed into a 35 cm^2^ square sponge immersed in saline solution (150 mMols of NaCl diluted in water Milli-Q). For stimulation, a gradual current ramp-up and ramp-down with 30-s duration will be used. Electrodes attached to the scalp will be supported by an elastic band. The electrodes (anode and cathode) will be connected to a battery-powered (9 v) stimulator with current verified by a precision digital multimeter (DT832, WeiHua Electronic Co., Ltd, China) with standard error of ±1.5%.

For ethical reasons, no changes will be made to HD routines (days and the place of sessions), clinical care (medicines, imaging, or blood exams), and previous prescription of painkillers or other medication.

### Outcome measures

This study will follow the outcome measures used in studies of multiday repetitive tDCS applied to the M1 or DLPFC to treat chronic pain and depression [17].

Data will be collected following assessments at baseline (week 2), immediately after the tenth day of intervention (week 6), and at 7- and 10-week follow-ups (Fig. 3). All evaluations will be performed by an experienced physical therapist blinded to group assignments. Socio-demographic and clinical characteristics will be collected from the participants and will include age, gender, ethnicity, marital status, level of education, income, time of HD, medication profile, and comorbidities.

**Fig. 3 Fig3:**
[figure not shown]
Schedule of enrollment, interventions, and assessments: Recommendations for Interventional Trials (SPIRIT). *VAS* Visual Analogue Scale, *MPQ* McGill Pain Questionnaire, *BDI* Beck Depression Inventory, *HAS* Hamilton Anxiety Scale, *KDQOL-SF* Kidney Disease Quality of Life—Short Form. *Post-intervention evaluation

The primary endpoint of the trial is pain assessed using the VAS pain score and McGill Pain Questionnaire (MPQ). Secondary outcome measures include depression anxiety, physical performance, and quality of life (QoL).

The pain VAS is a unidimensional measure of pain intensity, which has been widely used in diverse adult populations [18]. The pain VAS is a continuous scale consisting of a horizontal line, usually 10 cm (100 mm) in length, anchored by two verbal descriptors, one for each symptom extreme [18]. For pain intensity, the scale is most commonly anchored by “no pain” (score of 0) and “pain as bad as it could be” or “worst imaginable pain” (score of 100 [100-mm scale]). The VAS will be administered and the respondent will be asked to indicate the distance on the 0–100-mm line on the segmented scale that best describes their pain intensity over the last 24 h.

The MPQ is a multidimensional pain questionnaire designed to measure the sensory, affective, and evaluative aspects of pain and pain intensity in adults with chronic pain [18, 19]. The scale contains four subscales evaluating the sensory, affective and evaluative, and miscellaneous aspects of pain, responses to which comprise the Pain Rating Index, and a five-point pain intensity scale [18]. The MPQ is scored by hand by first counting the number of words selected to obtain a number of words chosen score (0–20 words). The Pain Rating Index provides a score ranging from 0 to 78 based on the rank values of the chosen words. The value (score) associated with each descriptor is based on its position or rank order in the word set, such that the first word is given a value of 1, the next a value of 2, and so on [18]. The Pain Rating Index contains 78 pain descriptor items categorized into 20 subclasses, each containing two to six words that fall into four major subscales: sensory (subclasses 1–10), affective (subclasses 11–15), evaluative (subclass 16), and miscellaneous (subclasses 17–20). There is also a one-item pain intensity scale [18]. The MPQ will be assessed by comparing means of total score between groups.

Depression levels will be assessed using the Beck Depression Inventory (BDI), a self-reporting tool of 21 questions relating to cognitive symptoms and attitudes [20]. For each question, patients choose one or more phrases that best describe how they felt in the previous week. The maximum score is 63 points, and high scores indicate severe depression [20]. Beck et al. suggest the following quantification scores for depression: a score of less than 10 indicates minimal or no depression, 10–18 signifies mild to moderate depression, 19–29 moderate to severe depression, and 30–63 severe depression [20]. For analysis, a total value of BDI of each group will be compared.

The severity of anxiety symptoms will be measured using the Hamilton Anxiety Scale (HAS) [21]. The HAS will be administered by an interviewer who asks a series of semi-structured questions related to symptoms of anxiety. The interviewer then will rate the individuals on a five-point scale for each of the 14 items. The values on the scale range from 0 to 4: 0 means that there is no anxiety, 1 indicates mild anxiety, 2 moderate anxiety, 3 severe anxiety, and 4 very severe or grossly disabling anxiety [21]. The total anxiety score ranges from 0 to 56. High levels are indicative of high anxiety.

Strength of the lower limbs will be evaluated by the 30-s chair stand test. A chair 43 cm high, with backrest, without armrest and a stopwatch will be used. Participants will be instructed to keep their arms crossed on their chest and to sit with their backs resting on the backrest. When the signal is given, the participant will stand up and return to the starting position as fast as possible in 30 s. The score corresponds to the number of times that the person is able to perform the complete movement in 30 s.

The arm curl test measures upper body strength and thus may contribute to aerobic fitness and arm muscle endurance. The 30-s arm curl test measures upper-body muscle function and is assessed by the number of arm curl repetitions performed with a 2-kg dumbbell during 30 s.

To assess the flexibility of the lower limbs (posterior thigh muscles), a sit and reach test will be performed. A chair 43 cm high and 50 cm of backrest will be used. During the test, participants will be instructed to sit on the edge of the chair with feet flat on the floor, knees and ankles at 90° flexion; then the dominant or painful leg will be stretched (hip and knee) with the calcaneus supported on the floor and with the ankle flexed at 90°. With overlapping hands and middle fingers on the same level, participants try to get as close as possible to their toes and hold that position for 2 s in three attempts, to get the arithmetic mean. A negative score will be recorded if the middle fingers do not reach the toes, and a score will be positive if the middle fingers were above the toes. Flexibility of the upper limbs will be performed using the scratch flexibility test. Participants will be instructed to pass one hand (dominant or more painful) over the shoulder to assess flexibility of the shoulder in flexion, abduction, and external rotation and to try to reach the other hand to assess extension, adduction, and internal rotation on the center of the back. Three replicates will be made to obtain the arithmetic mean of the results. The measurements will be made using a ruler, and the scores are considered negative if there is any distance between the middle fingers, and positive if the middle fingers overlap.

Timed Up and Go (TUG) test will be used to measure, in seconds, the time taken to stand up from a standard chair, walk 3 m, turn, walk back to the chair, and sit down. A chair with armrests and a seating depth of 44–47 cm is recommended [22]. Those who complete the test in less than 20 s tend to be independently mobile, able to get in and out of a chair without assistance, and climb stairs. The TUG test score correlates well with measures of gait speed, functional ability, and balance. An improvement of 1.4 s on the TUG test (within-patient change score) has been identified as the minimum clinically important difference [22].

The Kidney Disease Quality of Life—Short Form (KDQOL-SF) will be used to assess the QOL. This questionnaire is a specific instrument to evaluate patients on dialysis, applicable to all types of dialysis [23].

A total score for each physical test will be described by means and standard deviations. A total score of variables and all subscales will be compared within and between groups.

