**Methods/design:**

We describe a single-center, parallel-design, double blind randomized, sham-controlled trial. Forty-five subjects with CKD undergoing HD will be randomized to a motor cortex (M1), a dorso lateral prefrontal cortex (DLPFC), or a sham group. A total of ten sessions will be administered to participants over 4 weeks using a monophasic continuous current with an intensity of 2 mA for 20 min. Participants will be evaluated at baseline, immediately after the tenth session, and at 1 week and 4 weeks of follow-up after the intervention. Pain, depression, functionality, and quality of life will be evaluated.

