### Sample size

Sample size was estimated based on statistical considerations for a parallel trial and on previous studies that have paired noninvasive stimulation with chronic pain syndromes [9, 10, 15]. No previous studies have reported results about tDCS using a visual analog scale (VAS) or numeric rating scale (NRS) in CKD. G-Power 3.1.9.2 was used to calculate sample size. VAS is a 0–10-point scale and will be used as the primary outcome. Sample size calculation assumed a significance of 0.05 and power of 0.80. Fregni suggested in previous studies that a mean reduction of 3 points in VAS for the group under active stimulation was expected in contrast to no improvement in the sham group [15]. Sample size was estimated based on the assumption of significance of 0.05, power of 95%, with 0.40 effect size. According to this methodology the sample size would be 36 participants. We decided to add nine more patients to prevent any reduction of power in case of patient dropout. Thus, 45 patients will be recruited and randomized into three groups of 15 patients each.

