### Statistical analysis

Statistical analyses will use SPSS (v.19.0, Chicago, USA) and Graph Pad Prism 5. Clinical and sociodemographic characteristics (marital status, income, education, and ethnicity) will be described by means and standard deviations for continuous numeric parameters, and by frequency tables with 95% confidence intervals for categorical parameters. Chi-squared test will compare the distributions of categorical variables. Kruskal-Wallis test and ANOVA will compare differences in final values between groups.

The Shapiro-Wilk and Levene’s test will assess the normality of the distribution and homogeneity of variance of the data, respectively. Non-parametric tests will be used in case of non-normality distribution. Mauchly’s test of sphericity will be used to validate the correlation of the repeated measures and where the assumption of sphericity is violated, the Greenhouse-Geisser correction will be applied. The effects of stimulation on primary and secondary outcomes will be calculated using a mixed ANOVA model. The dependent variable will be the score of each outcome, and the independent fixed variables will be the time of treatment (baseline, tenth day, first follow-up, and second follow-up), the group of stimulation (active and sham), and the interaction term time vs group. Post-hoc comparisons will be carried out using Bonferroni correction for multiple comparisons.

Friedman test will be used for non-parametric data. Missing data will be treated by intention-to-treat analysis, taking into account the method of the last observation carried forward. Partial η^2^ will be calculated as measures of effect size in the ANOVA results (main effects and interaction effects). Partial η^2^ will be used to calculate the effect size, where η^2^ = 0.01 will be considered small, η^2^ = 0.06 moderate, and η^2^ = 0.14 large effect. Statistical significance will be set at *p* value less than 0.05.

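### The primary endpoint is VAS alone in one section and VAS with MPQ in another, with no success rule and no designated primary test, so the text does not fix the type I error rate

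*Protocol article*

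**What the plan says.** All references are to the protocol article.

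- **Sample size:** "VAS is a 0–10-point scale and will be used as the primary outcome". The only expected effect is a 3-point VAS reduction under active stimulation against none in sham. No MPQ effect is given. The calculation cites a significance level of 0.05, 95% power and an effect size of 0.40, and arrives at 36 participants, raised to 45 for dropout.
- **Outcome measures:** "The primary endpoint of the trial is pain assessed using the VAS pain score and McGill Pain Questionnaire (MPQ"). For the second instrument, "The MPQ will be assessed by comparing means of total score between groups". No sentence ranks the two instruments or says whether success needs one or both.
- **Assessment times:** after baseline, "immediately after the tenth day of intervention (week 6), and at 7- and 10-week follow-ups". The abstract gives the same schedule: "Participants will be evaluated at baseline, immediately after the tenth session, and at 1 week and 4 weeks of follow-up after the intervention". None of the three is named as primary.
- **Statistical analysis:** each outcome gets a mixed ANOVA with group, "the time of treatment (baseline, tenth day, first follow-up, and second follow-up") and their interaction. A separate sentence plans ANOVA or Kruskal-Wallis comparisons of final values between groups, without saying which visit is final. On multiplicity: "Post-hoc comparisons will be carried out using Bonferroni correction for multiple comparisons". Significance is set at p below 0.05.

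**The concern.** Two sections of one document define the primary endpoint differently. That is a contradiction, not detail left to a fuller analysis plan. It matters because the decision rule sets the error rate. A trial that may claim success on VAS or on MPQ, each at 0.05, has two chances of a false positive; a trial that requires both does not.

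The analysis section does not close the gap. It lists time, group and interaction as model terms and plans effect sizes for main and interaction effects, but says of no test that it decides the trial. Alongside these stands a second between-group test at an unspecified visit. With 15 patients per arm, and results meant to guide a larger multicentre study, the headline result could be chosen after the data are seen.

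**Working it through.** **1. Reproducing the plan's figure of 36.** The test family, number of measurements and within-patient correlation ρ are not stated, so the following is one reading. Take the time-by-group interaction in a repeated-measures ANOVA with k = 3 groups and m = 4 times, f = 0.40, α = 0.05, ρ = 0 and sphericity:

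λ = f²·N·m/(1−ρ), df1 = (k−1)(m−1), df2 = (N−k)(m−1)

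- N = 36: λ = 0.16 × 36 × 4 = 23.04, df = 6 and 99, power 0.9575.
- N = 33: λ = 0.16 × 33 × 4 = 21.12, df = 6 and 90, power 0.9365.

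In steps of three, 36 is the smallest N reaching 95%, and 36 + 9 = 45. The match is not unique: two times with ρ = 0 and 80% power also gives 36, while four times with ρ = 0.5 and 95% power gives 21.

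**2. Two outcomes, one test each.**

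- Either suffices, independent outcomes: 1 − (1 − 0.05)² = 0.0975.
- Both required: the error rate cannot exceed 0.05, because both tests must reject.

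**3. Null simulation of the planned design.** Inputs from the article: 15 per arm, three arms, four times, tests at 0.05. Assumptions: normal data, correlation 0.3–0.7 over time and 0–0.7 between outcomes, 20,000 runs per setting. The final-values test is taken as a one-way ANOVA at week 10.

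| Claim allowed if | False-positive rate |
|---|---|
| VAS interaction significant | 0.047–0.053 |
| VAS or MPQ interaction significant | about 0.08–0.10 |
| VAS interaction or VAS final values significant | about 0.08–0.10 |
| Either of these tests, on either outcome | about 0.14–0.19 |

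The first row shows that one interaction test covers all four times at about 0.05.

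**4. Post-hoc comparisons.** The Bonferroni family is not defined, so two readings were run under the same assumptions:

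- Six comparisons with sham within an outcome (2 contrasts × 3 times): 0.037–0.046 for VAS; 0.070–0.088 if either outcome counts.
- Three pairs at each time only: 0.071–0.088 for VAS; 0.126–0.165 if either outcome counts.

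**5. What candidate repairs do to sample size** (reading of step 1, f = 0.40 for each outcome):

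- VAS alone, interaction at 0.05: N stays 36.
- Either outcome at 0.025 each: overall error at most 0.05 (1 − 0.975² = 0.0494 if independent). Power is 0.923 at 36 and 0.976 at 45; 95% power needs 42.
- One visit tested by one-way ANOVA: λ = 0.16 × 36 = 5.76 gives power 0.525 at N = 36; λ = 0.16 × 45 = 7.2 gives 0.635 at N = 45. About 102 would be needed for 95%.

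**The case against.** The strongest reply is that the plan already handles the repeated assessments. The mixed ANOVA tests all four times together through one interaction term, so no visit has to be singled out to control error, and the post-hoc comparisons are Bonferroni-corrected. This stands. A reader might infer that three undesignated times make error control fail, or that six outcome-by-time tests can each be claimed at 0.05 (26.5% if independent: 1 − 0.95⁶). The documents do not support that: visit-specific comparisons enter as corrected post-hoc tests. The exposure that remains comes from the interaction not being named as the deciding test, the undefined final-values test and the undefined Bonferroni family.

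A second reply is that joining VAS and MPQ with *and* may mean that both must succeed, which inflates nothing, and that a fuller plan may state the rule. The first half is a possible reading, which is why the inflation is conditional. The second half does not remove the contradiction: one section names VAS alone, and the other names two instruments.

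A third reply is that this is a preliminary trial. That tempers the consequence, but the correction is only wording.

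**Conclusion.** The contradiction over the primary endpoint is certain. The supported conclusion is that the article does not fix the trial's error rate, not that error control has failed.

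- One interaction test per outcome, either outcome sufficient: about 8–10%, with 9.75% the figure for independence.
- Both outcomes required: no inflation.
- Final-values test admitted as a second route: about 8–10% for VAS alone and 14–19% for either outcome. These figures rest on the assumed correlations and on reading final as week 10.

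A reader might also infer that a single visit, such as the one after the tenth session, should be made primary. No passage favours one visit. Step 5 shows that such a choice, tested by one-way ANOVA with f = 0.40 at that visit, would require a new sample size.

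**What to change.** 1. In Outcome measures, name VAS as the sole primary outcome, in line with the Sample size section, and list MPQ as secondary.
2. In Statistical analysis, name the VAS time-by-group interaction, with group at its three randomized levels (the text now labels the factor only as active and sham), as the single primary test at 0.05.
3. State which visit *final values* means and which comparisons form the Bonferroni family. Label the final-values test and the visit-specific comparisons as supportive.

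If the sponsor wants both outcomes to stay primary, state the rule: both significant at 0.05, or either at 0.025. Under the reading that reproduces 36, the 0.025 option needs 42 for 95% power, which 45 covers if no more than three patients drop out (45 − 42 = 3).

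Cost: MPQ loses primary status. The changes are to wording only; data collection and the planned 45 patients do not change.

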### Statistical analysis

Statistical analyses will use SPSS (v.19.0, Chicago, USA) and Graph Pad Prism 5. Clinical and sociodemographic characteristics (marital status, income, education, and ethnicity) will be described by means and standard deviations for continuous numeric parameters, and by frequency tables with 95% confidence intervals for categorical parameters. Chi-squared test will compare the distributions of categorical variables. Kruskal-Wallis test and ANOVA will compare differences in final values between groups.

The Shapiro-Wilk and Levene’s test will assess the normality of the distribution and homogeneity of variance of the data, respectively. Non-parametric tests will be used in case of non-normality distribution. Mauchly’s test of sphericity will be used to validate the correlation of the repeated measures and where the assumption of sphericity is violated, the Greenhouse-Geisser correction will be applied. The effects of stimulation on primary and secondary outcomes will be calculated using a mixed ANOVA model. The dependent variable will be the score of each outcome, and the independent fixed variables will be the time of treatment (baseline, tenth day, first follow-up, and second follow-up), the group of stimulation (active and sham), and the interaction term time vs group. Post-hoc comparisons will be carried out using Bonferroni correction for multiple comparisons.

Friedman test will be used for non-parametric data. Missing data will be treated by intention-to-treat analysis, taking into account the method of the last observation carried forward. Partial η^2^ will be calculated as measures of effect size in the ANOVA results (main effects and interaction effects). Partial η^2^ will be used to calculate the effect size, where η^2^ = 0.01 will be considered small, η^2^ = 0.06 moderate, and η^2^ = 0.14 large effect. Statistical significance will be set at *p* value less than 0.05.

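### Baseline scores are collected but never used as a covariate: groups are compared on unadjusted final values, and the mixed ANOVA treats baseline as an outcome visit, so precision is lost

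*Protocol article*

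**What the plan says.** All of this is in the protocol article, Methods.

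- **Statistical analysis, first paragraph.** After the descriptive and chi-squared methods: "Kruskal-Wallis test and ANOVA will compare differences in final values between groups". No adjustment is mentioned.
- **Statistical analysis, second paragraph.** The effects of stimulation on primary and secondary outcomes come from a mixed ANOVA, in which "the independent fixed variables will be the time of treatment (baseline, tenth day, first follow-up, and second follow-up". The remaining terms are group and time-by-group. Post-hoc comparisons carry a Bonferroni correction. Non-parametric tests replace these methods if the data are not normal.
- **Statistical analysis, third paragraph.** The Friedman test is the non-parametric counterpart. Partial eta-squared is reported for main and interaction effects.
- **Outcome measures.** Every outcome is assessed at baseline, after the tenth session and at two follow-ups.
- **Sample size.** "Thus, 45 patients will be recruited and randomized into three groups of 15 patients each".

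Because the model terms are written out, the handling of baseline is a stated choice and not a detail left to an unseen analysis plan.

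**The concern.** Each planned analysis uses the baseline score in a weak way.

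- **Final values** ignore it. With 15 per arm, the standard error of a chance baseline difference between two arms is sqrt(2/15) = 0.37 SD. A difference above 0.5 SD in a given pair (z = 0.5/0.365 = 1.37) has a probability of about 17%, and this comparison does not correct for it.
- **The time-by-group term** uses baseline only implicitly, as a change from baseline. Change scores carry the full noise of the baseline measurement.
- **The group main effect** averages in a visit before treatment, where no effect can exist.

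What is at stake is precision in a 45-patient trial whose Discussion says it should guide a larger multicentre study. Such a study needs active-minus-sham differences in scale points with confidence intervals. Partial eta-squared does not supply them.

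**Working it through.** **Plan's own figure.** The Sample size section gives "Sample size was estimated based on the assumption of significance of 0.05, power of 95%, with 0.40 effect size" and then "According to this methodology the sample size would be 36 participants". Read as a three-group, four-visit within-between interaction with Cohen's f = 0.40, the noncentrality is f²·N·m/(1−ρ) = 0.16 × 36 × 4/1 = 23.04, with df 6 and 99. Power is 0.96 at N = 36 and 0.94 at N = 33, so 36 is reproduced. This needs an unstated between-visit correlation ρ of 0 and sphericity. At ρ = 0.3 or 0.5 the same formula gives 27 or 21. Other settings also return 36, so the reading is plausible but not certain.

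**Inputs for the precision check.** From the article: 15 per arm, three arms, four visits. Assumed, because the article does not give them: r between baseline and a later visit, equal SD at all visits, and equal correlation between all pairs of visits.

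**Variance of a between-arm difference at one visit** (final value = 1):
- change from baseline: 2(1 − r)
- baseline as covariate (ANCOVA): 1 − r²
- ANCOVA relative to change: (1 − r²)/[2(1 − r)] = (1 + r)/2

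| assumed r | change | ANCOVA | ANCOVA ÷ final | ANCOVA ÷ change |
|---|---|---|---|---|
| 0.2 | 1.60 | 0.96 | 0.96 | 0.60 |
| 0.3 | 1.40 | 0.91 | 0.91 | 0.65 |
| 0.5 | 1.00 | 0.75 | 0.75 | 0.75 |
| 0.7 | 0.60 | 0.51 | 0.51 | 0.85 |

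To match 45 patients under ANCOVA at r = 0.3/0.5/0.7, final values need about 45/(1 − r²) = 50/60/88 patients. Change needs about 45 × 2/(1 + r) = 69/60/53.

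**Dilution of the group main effect.** An effect of 0, 1, 1, 1 over four visits averages to 3/4.

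**Power of the tests.** Illustration: constant 1-SD effect in both active arms, 15 per arm, alpha 0.05. Group means (1, 1, 0) give 15 × 2/3 = 10. The noncentralities are:
- 6-df interaction: 10 × 0.75/(1 − r), df 6 and 126
- group main effect: 10 × 0.5625/[(1 + 3r)/4], df 2 and 42
- change of the three-visit mean: 10/[(1 + 2r)/3 + 1 − 2r], df 2 and 42
- ANCOVA, one visit: 10/(1 − r²), df 2 and 41
- ANCOVA, three-visit mean: 10/[(1 + 2r)/3 − r²], df 2 and 41

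| assumed r | 0.3 | 0.4 | 0.5 | 0.6 | 0.7 |
|---|---|---|---|---|---|
| interaction (planned) | 0.65 | 0.73 | 0.82 | 0.91 | 0.97 |
| group main effect (planned) | 0.85 | 0.79 | 0.74 | 0.69 | 0.64 |
| change, three-visit mean | 0.81 | 0.87 | 0.93 | 0.97 | 0.99 |
| ANCOVA, one visit | 0.82 | 0.85 | 0.89 | 0.94 | 0.98 |
| ANCOVA, three-visit mean | 0.99 | 0.99 | 0.99 | 1.00 | 1.00 |

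The adjusted three-visit mean is best throughout. Part of its lead comes from averaging visits and from using 2 df instead of 6, as the change row shows; the rest comes from the covariate. The adjusted single visit falls slightly below the group main effect at r = 0.3 and only matches the interaction at r = 0.7.

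**Cost of the covariate.** For two arms of 15, a 1-SD difference and alpha 0.025, final values have power 0.65. ANCOVA at r = 0.4/0.5/0.6 gives 0.73/0.78/0.85 if the covariate is treated as free. It gives about 0.71/0.76/0.83 once the lost df and the estimated slope are counted. At r = 0.2 it gives 0.65, which is no gain.

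**The case against.** **The named effect model already uses baseline.** The article assigns the effects of stimulation to the mixed ANOVA, and the role of the final-value comparison is unclear. In the time-by-group term a constant baseline imbalance cancels. This stands. A reader might infer that baseline is wasted altogether, or that the main analysis forgoes the whole gain of ANCOVA over final values (equivalent to 60 patients instead of 45 at r = 0.5). The documents do not support that. For the time-by-group term the relevant loss is ANCOVA against change, which is 35%/25%/15% of variance at r = 0.3/0.5/0.7 and shrinks as r rises.

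**The dilution to 3/4 affects only the group main effect.** This is correct. The article does not make that term the primary test, although it reports an effect size for it.

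**The omnibus test is not the only inference.** Bonferroni comparisons follow it, and the sample size may have been set for it. The 6 df also assume three group levels, while the article describes the group factor as active and sham, which would give 3 df. These points limit any charge that the interaction is useless. They do not supply a baseline-adjusted contrast.

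**The correlation is unknown.** Entry requires a VAS above 4, which restricts the baseline range and may lower r. If the sample size did assume a correlation of 0, ANCOVA would gain nothing over final values on that assumption, but its variance would be (1 + 0)/2 = 0.50 of the change contrast. So the size of the gain is conditional. Its direction against change is not, for any r below 1.

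**The planned analyses are valid.** Agreed. A reader might infer bias, but randomization protects against it.

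**Conclusion.** The point holds as a loss of precision, not as an error of validity. Neither planned analysis uses baseline as a covariate. At an assumed r of 0.3 to 0.7, adjustment removes 9% to 49% of the variance of the final-value comparison and 35% to 15% of the variance of the baseline-to-visit change contrast. At r of about 0.2 or less the gain over final values is immaterial once the covariate's cost is counted. These figures assume equal SDs and equal correlations across visits. The power figures also assume a constant 1-SD effect, which the article does not give. The change is recommended because it uses data already collected and costs almost nothing.

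**What to change.** Name one main analysis for each outcome. Model the three post-baseline visits with three-level group (M1, DLPFC, sham), visit, group-by-visit and the baseline score of the same outcome as covariate, optionally with baseline-by-visit. A constrained longitudinal model with a common baseline mean is an equivalent choice.

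- Report adjusted M1-sham and DLPFC-sham differences with 95% confidence intervals and the planned Bonferroni correction.
- State in advance whether these refer to one named visit (for example, immediately after the tenth session) or to the average over the three post-baseline visits. The Statistical analysis section names no primary visit, so this decision has to be made.
- If residuals are clearly non-normal, use a rank-based ANCOVA or a bootstrap or permutation version of the same model in place of unadjusted Kruskal-Wallis or Friedman tests.
- Apply the same model to depression, anxiety, the physical tests and quality of life.

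Cost: one degree of freedom for the covariate (more with baseline-by-visit), the choice of visit or average, and revised analysis wording. No patients, visits or measurements are added.
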